straightforward than for continuous outcomes. In fact, Spybrook and Raudenbush who developed the Optimal Design software stated: “In the case of a binary outcome, we do not typically standardize the model because the level-1 variance is heteroskedastic, which makes the meaning of the intraclass correlation,  $\rho$ , uninformative.” Our conservative approach will accommodate even large intraclass correlations. Aim 3’s selection of high and low performers is based on changes in facility-level overtreatment rates. We cannot be certain which facilities will choose to focus on hypoglycemia risk reduction as opposed to another Choosing Wisely topic area or none at all. Previous experience (courtesy of National Program Director for Medicine) suggests that a minimum of 4-6 VISNs will choose the hypoglycemia risk reduction focus, each with an average of 5 facilities. In addition, sites in other VISNs may implement this intervention. We obtained data from 2009 and 2010 to assess year to year variation. This allowed us to estimate power based on a paired  $t$  test for a simple pre-test post-test design. One hundred random samples of 20 facilities were chosen. The mean  $\pm 1$ SD change in overtreatment rate for the A1c <6% threshold, a level that puts patients at the highest risk was an absolute percent reduction of  $-0.9 \pm 2.4$ , e.g., an overtreatment rate falling from 10% to 9.1%. Based on paired  $t$  test, our study will require as few as 15 facilities to detect an absolute overtreatment rate reduction of 2.9, e.g., 10% to 7.1%, with 85% power, even assuming as little as 50% correlation between the SDs of each of the two measurements. This compares favorably with preliminary work from VISN 12 which showed that rates of overtreatment fell by 4.6 to 5.9 at the three A1c thresholds.

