
**Aim 1.** To assess the overall impact, both intended and unintended, of the Choosing Wisely Initiative.

H1.1. Patients treated in facilities that focus on hypoglycemia risk reduction will have a lower likelihood of overtreatment compared to those treated in other facilities.

H1.2. Patients treated in facilities that focus on hypoglycemia risk reduction will have the same likelihood of undertreatment compared to those treated in other facilities.

**Aim 2.** To assess the impact of commitment to quality, teaching intensity, and safety culture on patients' likelihood of overtreatment.

H 2.1a. Patients treated in facilities with higher levels of commitment to quality are less likely to be overtreated compared to those in facilities with lower levels of facility commitment to quality.

H2.1b. Patients treated in facilities with higher level of teaching intensity are less likely to be overtreated compared to those in facilities with lower level of teaching intensity.

H2.1c. Patients treated in facilities with higher level of safety culture are less likely to be overtreated compared to those in facilities with lower level of teaching intensity.

**Aim 3.** To identify configurations of the implementation strategy (Choosing Wisely toolkit), provider characteristics and organizational level factors that are associated with successful reduction of overtreatment rates by comparing high and low performers. Our sample size will be insufficient for formal hypothesis testing, but we will examine the following research questions using matrix and qualitative comparative analyses:

RQ3.1. Which configurations of the Choosing Wisely toolkit are associated with greater reduction in overtreatment rates?

RQ3.2. Which configurations of provider characteristics and organizational factors are associated with greater reduction in overtreatment rates?

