For Aim 1 we will use a hierarchical ordinal logistic regression approach using patient-level longitudinal data (4/1/14 to 3/31/2015) to model the probability of overtreatment (and undertreatment) in which Choosing Wisely Initiative participation status (focus on overtreatment of diabetes, overuse of MRI for low back pain, both, or neither) is the key predictor variable of interest. Using patient-level data will provide power to identify even modest differences between groups. Aim 2 will utilize similar methods to assess associations with the facility characteristics of commitment to quality, teaching intensity, and safety culture. Aim 3 will utilize facility-level (cross-sectional) aggregate data (4/1/13 to 3/31/2016). High and low performers will be identified based on changes in overtreatment rates pre- and post-initiative (rather than on absolute values). In order to minimize issues related to regression to the mean as well as floor and ceiling effects, we will focus on facilities that were mid-performing at baseline (2nd and 3rd quartiles). We will focus on those facilities which had high reductions in overtreatment rates at 12 months (high performers) and those who had low (or negative) reductions in overtreatment rates, i.e., got worse, (low performers). Surveys and phone interviews will be conducted to assess what practices were (or were not) implemented to reduce overtreatment, as well as what barriers and facilitators existed to following the initiative. (DM-QUERI has committed funds to support pre-funding work, including instrument refinement and testing - see support letter). Field testing will continue in year 1. The purpose of the surveys of high and low performing sites is to provide the data for the qualitative comparative analysis (QCA) to assess which factors contribute to the difference in performance. Data from semi-structured interviews and site visits will enhance the interpretation. At year 2, the findings of the QCA will be assessed in depth via site visits to the high performing sites, with artifact collection, procedural observation, and in person semi-structured interviews conducted with clinicians (including CPSs, PCPs, and clinic managers), to enhance understanding of contextual factors. Our overall approach is based on the methods developed and used by the

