**Aim 1.** To assess the *overall* impact, both intended and unintended, of the Choosing Wisely Initiative. All analyses will be conducted for various subgroups of high risk patients. Due to the nature of the outcome variable in the quantitative aims (Aims 1 and 2), the primary statistical technique for these two aims will be logistic regression. The “logit” (i.e., log of odds) of the presence of an event is regressed on a list of independent variables. We will use odds ratios (=exponentiation of the estimated regression coefficients) and their confidence intervals for the hypothesis testing. An odds ratio larger (smaller) than 1 with a 95% confidence interval not containing 1 indicates a higher (lower) likelihood of the occurrence of an event for the group in comparison relative to the reference group in an independent variable. In Aim 1 we will use multinomial logistic regressions to model the outcome variable, a polytomous variable. In the models the polytomous variable is treated as a nominal variable and a value in the variable is treated as the reference group; separate logistic regression models for the probabilities of non-reference groups against the reference group are constructed and estimated simultaneously. This approach is more efficient than separately conducting two logistic regression models (i.e., the overtreated versus those in moderate control and the

undertreated versus those in moderate control). The primary exposure variable in both H1.1 and H1.2 is the group indicator variable. Along with the previously listed independent variables, a patient's glycemic control status in the pre-initiation period will also be included in the models as a control variable. We will assess both the implementation and sustainability phases of the initiative.

**Aim 2.** To assess the impact of facility commitment to quality, teaching intensity, and safety culture on patients' likelihood of overtreatment. We will use a similar modeling strategy to Aim1 for this aim but employ binary logistic regression models, because the hypotheses focus on overtreatment (a binary variable: overtreatment versus moderate control). We will construct separate models for each of H2.1a, H2.1b, and H2.1c. We will also evaluate the associations among the three primary exposures variables in the hypotheses, and construct a statistical model including all three variables and compare with the separate models.

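### Section 2.4 names an ordinal model for Aim 1 and section 2.4.8 a nominal multinomial one; a standard ordinal fit could not test H1.1 and H1.2 separately

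*Protocol*

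**What the plan says.** Section 2 (Specific Aims) sets two hypotheses for Aim 1. Under H1.1, patients in facilities that focus on hypoglycemia risk "will have a lower likelihood of overtreatment compared to those treated in other facilities". Under H1.2, they "will have the same likelihood of undertreatment compared to those treated in other facilities".

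Section 2.4.5.1 defines the outcome from the last A1c value: below 6.5% is overtreatment, above 9.0% is undertreatment, and the range between is moderate control, which is to be the reference group.

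The model for this outcome is named twice.

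- Section 2.4 (Overview of Study Design and Timeline): "For Aim 1 we will use a hierarchical ordinal logistic regression approach using patient-level longitudinal data". Its stated purpose is "to model the probability of overtreatment (and undertreatment) in which Choosing Wisely Initiative participation status" is the key predictor.
- Section 2.4.8 (Aim 1): "In Aim 1 we will use multinomial logistic regressions to model the outcome variable, a polytomous variable". It continues: "In the models the polytomous variable is treated as a nominal variable and a value in the variable is treated as the reference group", and "separate logistic regression models for the probabilities of non-reference groups against the reference group are constructed and estimated simultaneously".

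Both statements are current text. Neither is labelled a sensitivity analysis, and the protocol does not mention proportional odds, a relaxation of that assumption, or a test of it.

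**The concern.** The three categories are ordered along A1c, so an ordinal model can be fitted to them, but it answers a different question from the nominal one. In the standard cumulative-logit model each participation contrast has one coefficient, shared by the cut-point at 6.5% and the cut-point at 9.0%. H1.1 needs that coefficient to differ from zero and H1.2 needs it to be zero, so the two hypotheses could not both be supported.

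What is at stake is mainly H1.2, which is there to detect an unintended loss of attention to poor control. Under a single-coefficient model, a fall in overtreatment would be reported as a rise in undertreatment whatever the data showed at the upper end. A protocol that names both models also lets an analyst choose between them after seeing the results while complying with the text either way.

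**Working it through.** **Inputs.** From section 2.4.4: reference-group overtreatment 0.290, and 0.273 as the detectable value with 300 patients per facility. From section 2.4.5.1: the three categories and the reference group. The protocol gives no undertreatment rate, so values of 3% to 20% are assumed. The protocol reports no result for the ordinal model, so there is no figure to reproduce.

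**Step 1: what proportional odds imposes.** With g = 1 for focus facilities and g = 0 otherwise,

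logit P(over) = a1 + b·g and logit P(over or moderate) = a2 + b·g, so logit P(under) = −(a2 + b·g).

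The odds ratio is exp(b) for overtreatment and exp(−b) for undertreatment; each is the inverse of the other.

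For the protocol's contrast: (0.273/0.727) / (0.290/0.710) = 0.3755/0.4085 = 0.919. The forced undertreatment odds ratio is 1/0.919 = 1.088. An assumed 10.0% undertreatment rate would therefore become 10.8%.

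**Step 2: what the fitted model reports if undertreatment does not change.** I maximised the proportional-odds likelihood for population probabilities (0.290, 0.710 − u, u) against (0.273, 0.727 − u, u). The groups have equal weight, and there are no covariates or random effects.

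| Assumed u | Undertreatment forced by step 1 | Fitted common OR | Fitted undertreatment (truth: no change) |
|---|---|---|---|
| 3% | 3.25% | 0.927 | 2.9% to 3.1% |
| 5% | 5.41% | 0.931 | 4.8% to 5.2% |
| 10% | 10.78% | 0.940 | 9.7% to 10.3% |
| 15% | 16.10% | 0.947 | 14.7% to 15.4% |
| 20% | 21.38% | 0.952 | 19.6% to 20.4% |

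In every row the odds ratio is closer to 1 than the true 0.919, and undertreatment appears to rise when it has not. At u = 10% the fitted fall in overtreatment is 28.8% to 27.5%, against a true 29.0% to 27.3%.

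**Step 3: the nominal model on the same truth.** With two logits against moderate control, the odds ratios are:

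- over versus moderate: (0.273/(0.727 − u)) / (0.290/(0.710 − u))
- under versus moderate: (u/(0.727 − u)) / (u/(0.710 − u)) = (0.710 − u)/(0.727 − u)

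At u = 10% these are (0.273/0.627)/(0.290/0.610) = 0.916 and 0.610/0.627 = 0.973. Across u = 3% to 20% they run from 0.918 to 0.911 and from 0.976 to 0.968. No rise in undertreatment is imposed. However, the undertreatment odds ratio is not exactly 1 when the undertreatment probability is unchanged, because patients leaving overtreatment enlarge the reference category.

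**Step 4: which model the rest of the text fits.** A middle category can be the reference in a nominal model; it has no such role in a cumulative one. Sections 2.4.5.1 and 2.4.8 therefore agree with each other, and section 2.4 stands alone.

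**The case against.** The strongest reply is that the operative text is already right. Section 2.4 is an overview and gives the model part of one sentence. Section 2.4.8 sets out the nominal model, its reference category and its two simultaneous logits, explains why this is preferred to separate regressions, and names participation as the exposure for both H1.1 and H1.2. An analyst working from the analysis section would fit a model that separates the hypotheses. This stands, and it sets the severity.

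The reply also notes that ordinal need not mean proportional odds. A partial or non-proportional version allows separate coefficients at the two cut-points and escapes the result in step 1. This stands too, although the protocol specifies no such version.

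A reader might go further and infer that the plan as written decides H1.2 by model form. The documents do not support that: it requires both that the overview wording prevails over section 2.4.8 and that a single common coefficient is meant.

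A reader might also infer that a real benefit could almost vanish. The fitted common odds ratio does reach 0.967 if undertreatment falls from an assumed 10% to 9%, and 0.987 if both tails fall by 1.7 points. But the protocol does not hypothesise a fall in undertreatment: H1.2 says no difference, and the worry stated in section 2 is a rise. The range in step 2 is the fair measure.

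None of this removes the conflict between two current statements of the primary model.

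**Conclusion.** The contradiction is real and the protocol does not resolve it. Its consequence is conditional. If section 2.4 were followed with a standard proportional-odds model, an overtreatment odds ratio of 0.919 would force 1.088 for undertreatment. With undertreatment truly unchanged, the common odds ratio would be 0.927 to 0.952, with a spurious rise in undertreatment. The sizes rest on assumed undertreatment rates of 3% to 20% and a simplified fit without clustering or covariates. The reciprocal constraint in step 1 does not depend on those assumptions, and the spurious rise appears at every rate tried.

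Because section 2.4.8 describes a suitable analysis and section 2.4.5.1 agrees with it, this is a consistency correction to the stated primary model. It should be made before analysis, but it does not call the design, the data or the section 2.4.8 analysis into question.

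**What to change.** 1. In section 2.4, replace the ordinal model with a hierarchical multinomial (generalised logit) regression, matching section 2.4.8.
2. In section 2.4.8, state that H1.1 rests on the participation contrasts in the overtreatment logit and H1.2 on those in the undertreatment logit. Participation has four levels, so there are three contrasts per logit.
3. Because the undertreatment logit is relative to moderate control (odds ratio about 0.97 when undertreatment stays at an assumed 10% and overtreatment falls to 0.273), judge H1.2 on the model-based undertreatment probability, or on undertreatment versus all other patients.

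The cost is a few sentences and no new data. The multinomial model carries a second set of coefficients, and possibly random effects for each logit, but section 2.4.8 already commits to that model. With about 205,000 high-risk patients in 2009 (section 2.4.4), the extra parameters should matter little.

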**2. Specific Aims.** Implementation of practice change is difficult and large scale implementation is particularly difficult. Among the challenges facing the healthcare system in general and healthcare organizations such as VHA is the overuse of low value care. Reducing low value care has become a recent focus of VA's quality improvement efforts as evidenced by the VA's creation of a Choosing Wisely Taskforce to recommend how this national initiative can be implemented. Improving medication safety also constitutes an attempt to reduce low value or potentially harmful care. Critical issues of overuse of low value practices and medication safety intersect in overtreatment of diabetes (DM). Specifically, (over)intensive glycemic control increases hypoglycemia risk and morbidity without providing meaningful benefit. Our work indicates that among patients with diabetes who are at high risk for hypoglycemia – due to use of specific hypoglycemic agents, age, and/or significant comorbidities – up to 50% are potentially overtreated, as defined by an A1c <7%. National recognition for hypoglycemic safety is evidenced by the creation of a Health and Human Services Federal Interagency Workgroup (with representatives from VA and DoD) to address adverse drug events, including those from hypoglycemic agents. Moreover, the Choosing Wisely Initiative to reduce low value care led by the American Board of Internal Medicine Foundation includes an American Geriatric Society recommendation to “not treat most persons over 65 years of age with medications to reduce the A1c<7.5%.” For most physicians this involves changes to their current clinical practice. VHA's soon to be announced response to the Choosing Wisely Initiative will include hypoglycemic safety as one of its targeted conditions (see letters of support from [name]). Our goal is to study the implementation of the Choosing Wisely Initiative as it plays out at the facility and practitioner levels. We will assess the concomitant implementation of processes of reducing clinically inappropriately tight glycemic control (de-implementation) as well as assess the effectiveness of a toolkit being promoted by this initiative. Because focus on this initiative could have the unintended consequence of paying less attention to poor glycemic control (A1c>9%), we will also assess undertreatment. In so doing, we will inform both VHA and the broader federal health community. We propose three specific aims and associated hypotheses (H) and research questions (RQ):

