**2.4.3. Study Populations.** The population for Aims 1 and 2 will be VHA clinic Veteran users with diabetes receiving insulin and/or sulfonylurea treatment in the time period 4/1/14 to 3/31/2015 (the initiative start date being 4/1/2014). A Veteran is determined to have diabetes if one has VHA service use in the year and has two or more visits with diabetes ICD-9-CM codes (250.XX) from inpatient or outpatient (face-to-face) care over a two year period or has prescriptions for diabetes medication in the year. Aims 1 and 2 will utilize longitudinal data from Veterans with diabetes who have at least 1 A1c value. For our primary outcome measure of overtreatment (see below), we will include patients having at least one of the following additional criteria: age >75 years, last serum creatinine  $\geq 2.0$  mg/dl, or an ICD-9-CM diagnosis of cognitive impairment or dementia in ambulatory care. From a population health perspective, individuals 75 years of age and older have limited life expectancy and an increased co-morbid illness burden, and thus have decreased life-time benefit and increased risk from intensive glycemic control. Impaired renal function affects metabolism of oral hypoglycemic agents and insulin. In the ACCORD trial, subjects with serum creatinine levels between 1.0 and 1.3 mg/dl had greater risk of serious hypoglycemia than those with normal creatinine levels (<1.0 mg/dl); subjects with creatinine >1.3 mg/dl had even greater risk. To be conservative, we have restricted our measure to even worse renal function. As a sensitivity analysis, we will evaluate patients with age greater than 70 years or a serum creatinine > 1.7 mg/dl. Cognitive impairment may adversely affect patients' ability to self-manage their diabetes and is associated with increased risk of serious hypoglycemia in both the control and intensive treatment arms of the ACCORD trial.

**2.4.4. Power Analysis.** Power calculation in hierarchical/multi-level models is not straightforward and there are no established norms. The power calculation for such models needs to consider sample sizes in all levels involved. For a two-level model, a rule of 30 groups and 30 subjects per group is usually recommended to ensure sufficient power for fixed effects. Using Optimal Design® software, we conducted power analyses for detecting

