## 2.4.5. Dependent and Independent Variables (Quantitative)

### 2.4.5.1. Dependent Variables (Outcome Measures for Summative Evaluation)

**Overtreatment and undertreatment.** Using the last A1c value in a time period we will define overtreatment if it is less than the thresholds of 6.5% (we will evaluate 6.0% and 7.0% for sensitivity analysis). If the same A1c value is greater than 9.0%, it is considered undertreatment. Those in the range of 6.5% to 9.0% are considered to be in moderate glycemic control and will be used as the reference group in statistical analyses.

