in the initiative, we will seek positive deviants, i.e., facilities which are statistically higher performers than other facilities in the same VISN. Positive deviants may provide special insights into successful implementation

strategies. We will identify them as we have done previously using a statistical approach recommended by the National Committee of Quality Assurance. In order to characterize these sites further as to their performance over time, we will also examine facility rates at baseline and at 2 years following the start of the intervention. Rates at 2 years will provide information about sustainability of improvement. We note that this study sample is a dynamic cohort since new members are added as they meet the study criteria.

**2.4.7. Quantitative Data Sources and Collection.** We will obtain VHA data from Corporate Data Warehouse (CDW), a national repository of data, and other VA files. The goal at VA has been to transition most VA data to reside on CDW servers. We will include files containing patient characteristics, outpatient and inpatient encounters, diagnosis and procedure codes, pharmacy/prescription information, and laboratory (A1c and serum creatinine) values from 2012 to 2016. We will use CMS data (when available), which includes Medicare (for outpatient and inpatient encounters, diagnosis and procedure codes, eligibility status) and Medicaid (for additional pharmacy/prescription information), as we have done previously. Data for commitment to quality, safety culture, and teaching intensity are described above (2.4.5.2). Specific data files are described below:

**Patient Medical Encounter Data** include file records for all VA inpatient and long-term stays and all outpatient visits, with information on patient characteristics, eligibility, type of care, and multiple codes for diagnoses (ICD-9-CM codes) and procedures (ICD-9-E or CPT4 codes). They are VHA Medical ASA (MEDSAS) datasets.

**VA Laboratory Data** are recorded at each site for all tests performed and subsets are extracted to national databases. We recognize that not all patients in our study will have results available from laboratory tests. In our prior work, we have found that, based on CPT codes, most VHA patients with diabetes receive the majority of their outpatient laboratory tests in VA clinics, and have regular measures of A1C and creatinine.

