**Pharmacy Records** will be obtained from the Pharmacy Benefits Management Strategic Health Group (PBM). This national VA prescription database includes information on specific medications, including dates, duration, dose, and physician instructions. The PBM uses a verification process to assure data accuracy and completeness. Use of non-VA pharmacy services by VA patients is not included in PBM. To address this potential limitation, we will include data from Medicare Part D and Medicaid prescription records (if available). We note that such information may not be available for the entire study period due to time lags.

**2.4.8. Quantitative Data Statistical Analyses.** We will begin all analyses with inspection of frequency distributions and bivariate analyses of means (t-tests and ANOVAs) and proportions (Chi-square tests) among subgroups defined by our independent variables, and will use graphical methods for exploratory data analysis. We will enter variables into statistical models according to our conceptual framework and hypotheses. Cells in the cross tables with 0 or small numbers will be collapsed with other cells. In handling variables with missing data, the primary analyses will be restricted to those with values (complete case analysis); alternatively, patients with unknown values for a variable will be grouped into a subcategory to be included in the statistical models. Our analyses need to account for the possibility that observations may not be completely independent due to individuals nested within a VA facility, and VA facilities nested within a VISN. We will use hierarchical modeling (also termed multi-level models/mixed effects models/random-effects models) for the analysis of correlated data to address the issue of possible underestimation of variance for regression coefficient estimates under conventional regression models. In the statistical models, facilities and VISNs will be considered as random effects. Other than the primary exposure variable specified in each hypothesis, independent variables will also be included in the statistical models as control variables.

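### Aim 1 keeps only patients with an A1c after the initiative starts, so differences in testing between facility groups could mask or exaggerate a difference in undertreatment (H1.2)

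*Protocol*

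**What the plan says.** Four parts of the protocol bear on this point.

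- **Purpose (section 2, Specific Aims).** Undertreatment is measured as a check on harm: "Because focus on this initiative could have the unintended consequence of paying less attention to poor glycemic control (A1c>9%), we will also assess undertreatment". H1.2 expects the same likelihood of undertreatment in focus facilities as elsewhere.
- **Eligibility (2.4.3).** The population is patients "receiving insulin and/or sulfonylurea treatment in the time period 4/1/14 to 3/31/2015 (the initiative start date being 4/1/2014". In addition, "Aims 1 and 2 will utilize longitudinal data from Veterans with diabetes who have at least 1 A1c value".
- **Outcome (2.4.5.1).** "Using the last A1c value in a time period we will define overtreatment if it is less than the thresholds of 6.5" per cent. "If the same A1c value is greater than 9.0%, it is considered undertreatment". Values from 6.5% to 9.0% form the reference category. There is no category for a patient without a value.
- **Missing data (2.4.8).** For variables with missing data, "the primary analyses will be restricted to those with values (complete case analysis"). The stated alternative is this: "alternatively, patients with unknown values for a variable will be grouped into a subcategory to be included in the statistical models".

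Two further statements qualify the picture. Section 2.4.7 concedes that "We recognize that not all patients in our study will have results available from laboratory tests", but adds that most VHA patients with diabetes have A1c and creatinine measured regularly. Under Aim 1, section 2.4.8 puts each patient's glycemic control status before the initiative into the model as a covariate.

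**The concern.** The study period opens on the day the initiative starts, so having an outcome A1c is itself a post-exposure event. The analysis conditions on that event.

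This matters most for H1.2. The feared harm is that poor control gets less attention, and ordering fewer A1c tests is one plausible form of less attention. A patient above 9% who goes the whole period untested is in neither the numerator nor the denominator of the undertreatment comparison. If this happens more often in focus facilities, undertreatment there is understated and the result moves towards the hypothesised finding of no difference. If the initiative instead prompts more testing of poorly controlled patients, the same mechanism works in reverse and a difference is exaggerated. The protocol names no comparison of testing between the four facility groups that would reveal either.

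**Working it through.** The protocol gives no testing rate, no undertreatment rate and no untested share, so there is no plan figure to reproduce. All testing and undertreatment rates below are assumptions chosen to show the mechanism.

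**Step 1. Who is lost.** The eligibility sentence in 2.4.3 does not say in which window the A1c must fall.
- If it means the study period, an untested patient is excluded at entry.
- If any A1c counts, the patient enters, but the outcome in 2.4.5.1 is missing and the primary rule in 2.4.8 drops the patient.

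The primary analysis is the same either way. The alternative rule speaks of unknown values for a variable and is not said to apply to the outcome. On the first reading no such patient is left to be categorised.

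**Step 2. Effect on the odds ratio.** Let u be the true share above 9%, t_u the share tested among those patients, and t_0 the share tested among the rest.

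Observed rate = u·t_u / [u·t_u + (1 − u)·t_0]

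The observed odds equal the true odds times t_u/t_0. The odds ratio between facility groups is therefore multiplied by (t_u/t_0 in focus facilities) ÷ (t_u/t_0 elsewhere). If that ratio is equal in all groups, the odds ratio is unbiased although the absolute rates are not. In the planned multinomial model the same holds with t_0 read as testing in the 6.5–9.0% category.

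**Step 3. Crude illustration.** Assume u = 10% in both groups, t_0 = 0.95 everywhere, and t_u = 0.95 in the other facilities.

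| t_u in focus facilities | Observed rate there | Factor on odds ratio | True focus rate that would show as OR 1.00 |
|---|---|---|---|
| 0.90 | 0.090/0.945 = 9.5% | 0.90/0.95 = 0.947 | 10.5% |
| 0.85 | 0.085/0.940 = 9.0% | 0.85/0.95 = 0.895 | 11.0% |
| 0.75 | 0.075/0.930 = 8.1% | 0.75/0.95 = 0.789 | 12.3% |

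The factors do not depend on u. The direction can reverse: with t_0 = 0.90 everywhere and t_u rising from 0.90 to 0.95 in focus facilities only, the factor is 0.95/0.90 = 1.056.

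**Step 4. What adjustment for prior status removes.** Assume 10% of patients had a prior A1c above 9%, with outcome rates of 50% in them and 4% in the rest, and 90% testing throughout.
- True overall rate: 0.10 × 0.50 + 0.90 × 0.04 = 8.6%.
- Cut testing of the prior->9% patients to 79%. Tested shares become 0.10 × 0.79 = 0.079 and 0.90 × 0.90 = 0.810, total 0.889.
- Crude observed rate: (0.079 × 0.50 + 0.810 × 0.04)/0.889 = 0.0719/0.889 = 8.1%.
- Rates within strata: still 50% and 4%.

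If testing depends only on facility group and prior status, the adjusted odds ratio is therefore unbiased, given a correctly specified model. The factor in Step 2 then has to be applied within each prior-status stratum. It differs from 1 only where testing also tracks current control, and does so differently by facility group. Patients with no prior value are a separate loss, because the complete-case rule drops them on the covariate as well.

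**Step 5. Bounds on an absolute rate.** With observed rate r and untested share m, the true rate lies between r(1 − m) and r(1 − m) + m. For r = 10% this gives 9.8–11.8% (m = 2%), 9.5–14.5% (m = 5%) and 9.0–19.0% (m = 10%).

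**The case against.** The strongest reply is the prior-status covariate. The natural example, a patient last seen at 10% who then goes untested, is one of neglect acting through the known earlier value. Step 4 shows that adjustment deals with this. That part of the objection stands, and it means the crude figures in Step 3 overstate what would carry through if testing were driven mainly by prior status.

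Other points also have force.
- These are patients in care: 2.4.3 requires VHA use and insulin or sulfonylurea treatment, one A1c is enough, and 2.4.7 says most are tested regularly. But that describes average practice, not testing by current control or by facility group after the start.
- A patient who rises above 9% and is tested is still captured. Only the part of reduced attention that shows as no test at all is lost.
- The initiative is itself centred on A1c, with clinical reminders and audit and feedback named in 2.4.10, so testing in focus facilities could rise. This is why the direction must be left open.
- The statistical analysis plan is not at hand and may add sensitivity analyses. The point here, however, concerns eligibility, outcome categories and a primary missing-data rule that the protocol itself fixes.

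A reader might infer that the plan removes poorly controlled patients and so hides undertreatment. The documents do not support that. They give no testing rate by control status or by facility group, and they do not say that less testing is how reduced attention would appear.

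**Conclusion.** The point holds as a possibility that the design leaves unchecked, not as a demonstrated bias. Eligibility, outcome and the complete-case rule together condition Aim 1 on a post-initiative A1c. Adjustment for pre-initiation status removes the part of the selection explained by prior control. Two parts remain: selection on current control within prior-status strata that differs by facility group, and the loss of patients with no prior value.

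The size is unknown. Under the assumptions of Step 3, applied within strata, a fall of 5 to 20 points from 95% testing would multiply the odds ratio by 0.95 to 0.79. A rise in testing of poorly controlled patients would push it above its true value. No figure in the protocol is contradicted. The change is worth making because it costs little and protects H1.2, the protocol's check on unintended harm, from false reassurance.

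**What to change.** 1. In 2.4.3, define the Aim 1 cohort by the diabetes, drug and risk criteria, without requiring an A1c in the outcome period.
2. In 2.4.8, keep the planned complete-case multinomial model as primary.
3. Beside H1.2, report the share with no outcome-period A1c by facility group, overall and by pre-initiation status, above all among patients whose prior A1c was above 9%.
4. Add a sensitivity analysis with no A1c in the period as a fourth nominal outcome category. Weighting for the probability of being tested, or bounds as in Step 5, are acceptable alternatives.
5. Do not carry the prior category forward for untested patients. That assumes no change in the quantity under study, and it fails for new entrants to the dynamic cohort described in 2.4.6.

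The cost is a rewording of two sections, one table and one extra model. Laboratory data for 2012 to 2016 are already to be extracted (2.4.7), the Aim 1 outcome is already treated as nominal, and prior status is already a covariate. One small downside is that some untested patients will have had laboratory work outside VA. The untested category should therefore be reported by itself and not counted as undertreatment. Medicare procedure codes, where available, could help identify outside testing.
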